#### Sampling and population

In ITS studies, sample size calculations are related to the estimation of the number of observations or time points at which data will be collected. According to Ramsey *et al.*'s quality criteria for ITS designs, at least 10 pre- and 10 post-data points would be needed to reach at least 80% power to detect a change (if the autocorrelation is >0.4) [27]. Since the current study is a pilot, it is not known what the autocorrelation might be or what effect size the intervention is likely to produce. We therefore decided to use a relatively large number of data points to ensure that any trend or seasonal differences can be detected: 52 data points per site (where one data point = two-week segment)--26 data points before the introduction of the intervention (equivalent to 12 months' worth of two-week segments) and 26 data points after the introduction of the intervention (two-week segments for 12 months). Participants will be family physicians practicing in a solo or group practice within the Hamilton FHT and their patients at risk for osteoporosis selected according to gender- and age-eligibility criteria (*i.e.*, women ≥50 years of age, men ≥65 years of age).

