#### Analysis

Results of this ITS study will focus on the impact of the intervention on the time series, which will be tested by comparing pre- and postintervention segments of the time series to estimate the magnitude and form of the impact. "Impact" on practice will be defined according to the level of change that is observed between the baseline and postintervention periods of the study. The impact of the tool for changing practice and satisfaction with the tool will also be analyzed across the three sites. Aggregated data from each two-week segment period on primary outcomes will be analyzed using the autoregressive integrated moving average (ARIMA) approach and time-series regression models [28,29]. We hypothesize that the 26 time-point baseline assessment of practice will show no pre-intervention trend. The ARIMA approach will estimate the extent to which a significant level of change occurs between the pre-intervention and postintervention phases of the study. The multiple measurement points are necessary for the ARIMA analysis to distinguish between treatment effects and secular trends. The advantage of using the ARIMA approach for analysis is that it accounts for the three major sources of noise that may confound the analysis: trend, seasonality, and random error [28,29]. Secondary outcomes and logs of patient-initiated data from tablet PCs will be analyzed using frequency analysis of site-specific data, descriptive and inferential statistics to calculate proportions and time to completion of the RAQ (*e.g.*, means with standard deviations), and independent-sample *t*-tests or analysis of variance (ANOVA) for group comparisons (*e.g.*, differences between sites for outcomes).

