### Control of the implementation of the intervention

We anticipate that once the intervention is implemented, there will be an increase trend toward optimal practice according to guidelines. This sudden rise will likely occur from the implementation process rather than the intervention itself. We therefore chose a greater number of data points (which is also equal to the data points in the baseline assessment phase) to help neutralize the initial impact of the implementation and allow the true impact of the intervention to emerge.

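### The expected go-live rise is to be controlled only by having more data points, which dilute an early transient without removing it, so part of it is counted as impact

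*Protocol article*

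**What the plan says.** Under 'Control of the implementation of the intervention' (Potential limitations), the authors anticipate that "once the intervention is implemented, there will be an increase trend toward optimal practice according to guidelines". They then attribute the jump: "This sudden rise will likely occur from the implementation process rather than the intervention itself". The control offered is a greater number of data points, equal to the number at baseline, "to help neutralize the initial impact of the implementation and allow the true impact of the intervention to emerge".

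Under 'Sampling and population' the series has "52 data points per site (where one data point = two-week segment"), of which "26 data points after the introduction of the intervention (two-week segments for 12 months"). The reason given there for the number is different: "to ensure that any trend or seasonal differences can be detected".

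Under 'Analysis' (Phase 2) the test consists of "comparing pre- and postintervention segments of the time series to estimate the magnitude and form of the impact". Impact "will be defined according to the level of change that is observed between the baseline and postintervention periods" of the study. ARIMA and time-series regression are named, and ARIMA is credited with handling trend, seasonality and random error. No transition period, early window or temporary-effect term is stated.

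**The concern.** The limitations section identifies a specific disturbance that is probably not the tool's effect. It is locked to the date of introduction, so it falls inside the post series and shares its onset with the effect being estimated. Trend, seasonality and random error are different things, and adjusting for them does not separate it out. Adding observations reduces variance. It reduces bias from a transient only by averaging it over a longer period, and by how much depends on the model.

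What is at stake is the reading of the pilot. The article says such a study should show whether wider testing is justified and inform a later randomized trial. An estimate that carries part of the go-live rise would make the tool look better than it is on the plan's own account of that rise.

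**Working it through.** **Inputs from the document.** Twelve months at two weeks per segment is 52/2 = 26 points; 26 + 26 = 52 per site, as stated. The autocorrelation and effect size are declared unknown, and no height or duration is given for the rise.

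**Assumptions.** The true tool effect is zero. The transient in post segment k (k = 0 to 25) is A·2^(−k/h), with half-life h of 2, 4 or 8 segments (4, 8 or 16 weeks). Errors are white noise unless stated.

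**1. Single-step model.** The bias is the mean of the transient over the post period:

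A/26 × (1 − 2^(−26/h)) / (1 − 2^(−1/h))

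- h = 2: 3.414/26 = 0.13A
- h = 4: (0.9890/0.1591)/26 = 6.216/26 = 0.24A
- h = 8: (0.8949/0.0830)/26 = 10.78/26 = 0.41A

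**2. Models with a slope.** In a model with a level change and a slope change, the level bias is the intercept from least squares of the transient on (1, k).

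| Half-life (segments) | Step only | Level + post-slope | Step + one linear trend |
|---|---|---|---|
| 2 | 0.13A | 0.43A | 0.44A |
| 4 | 0.24A | 0.64A | 0.65A |
| 8 | 0.41A | 0.83A | 0.85A |

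The level-plus-slope model also fits a spurious fall of 0.59A to 0.83A over the post year.

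**3. What more points achieve.** At half-life 4, going from 10 to 26 post points lowers the step bias from 0.52A to 0.24A and the level bias from 0.90A to 0.64A. The help is real but partial.

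**4. Other shape and autocorrelation.** For a flat block of 2, 4 or 6 segments, the step bias is 2/26, 4/26 or 6/26, that is 0.08A, 0.15A or 0.23A. The level bias with a post-slope is 0.28A, 0.53A or 0.74A. With AR(1) = 0.4 these become 0.15A, 0.22A and 0.29A (step) and 0.46A, 0.64A and 0.80A (level). The bias was upward in every case tried.

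**5. Consequence for a two-sided 5% test.** With white noise the SE of the step is √(1/26 + 1/26) = 0.277 residual SD; that of the segmented level term is 0.555 SD. For A = 2 SD and h = 4, the bias is 0.48/0.277 = 1.7 SE (step) or 1.28/0.555 = 2.3 SE (level). Positive rates by simulation, with the residual variance estimated and no tool effect:

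| A | Half-life | Step | Level (with slopes) |
|---|---|---|---|
| 1 SD | 2 | 7% | 11% |
| 1 SD | 4 | 13% | 20% |
| 2 SD | 2 | 13% | 30% |
| 2 SD | 4 | 34% | 60% |

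**The case against.** Four points can be made for the plan.

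- **The text is hedged.** The rise is only likely to come from implementation, and more points are only said to help. In a step model most of a short transient is indeed averaged away. This stands: a reader might infer that the whole rise is booked as tool effect, or that no positive result could be attributed to the tool, and the document supports neither.
- **The analysis is to estimate the form of the impact.** In ARIMA intervention analysis that can cover temporary as well as permanent change, and a fuller plan may specify such a term. So a reader who infers a flat contradiction between the limitations section and the analysis section goes too far. But compatibility is not commitment. The control the article actually names is the number of points.
- **Phase 1 is a run-in.** Clinics use the tool under observation before it counts as implemented, which may absorb some disturbance. The criterion is technical, however (one week without new problems), and the limitations section still expects the rise after implementation without invoking that run-in.
- **The largest figures are model-dependent.** The article specifies no post-slope, so it cannot be said that the planned analysis will show a false fading of benefit; that holds only if a slope change is fitted. The level bias is not confined to that model: a single linear trend, which an analysis meant to separate secular trends might well include, gives almost the same bias.

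**Conclusion.** The point holds in a limited form. The issue is a stated remedy that does not do what is claimed for it, rather than a missing detail. The number of points dilutes an early transient, and the remainder enters the level change that is called impact. The size depends on a height, duration and error structure that the document does not give. Over the half-lives tried, the remainder is roughly an eighth to two fifths of the initial height in a step model, and more than two fifths to over four fifths once a slope is in the model. False-positive rates are close to nominal for a small, short rise in a step model and high for a large or slow one, so no single rate should be quoted. For a pilot this should be corrected, but it does not invalidate the design.

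**What to change.** In 'Analysis' and in 'Control of the implementation of the intervention':

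1. Before any post data are seen, fix an early window, for example the first 4 to 6 segments (8 to 12 weeks), and give it its own indicator.
2. Define primary impact as the change in the remaining post segments against baseline.
3. Report the early-window change and the all-segments estimate alongside.
4. Replace the claim that the number of points neutralizes the rise with a statement that more points only dilute it.

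**Cost.** No extra data are needed. Without a trend term and with white noise, the SE ratio is √(1/26 + 1/22)/√(2/26) = 1.04 for 4 segments and √(1/26 + 1/20)/√(2/26) = 1.07 for 6. Over AR(1) from 0 to 0.4 the increase is about 4–9%. With a linear trend it is about 16–28%.

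**What it buys.** With a 6-segment window, no trend and white noise, the remaining bias is 0.02A, 0.11A or 0.29A for half-lives 2, 4 or 8. With a linear trend it is 0.10A, 0.28A or 0.53A. A slow decay is therefore only partly removed, and the text should say so. The window length is a judgement; a transient that ends within it leaves no bias.

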### Instability

Although the ITS design is susceptible to fluctuating trends and cycles, most of these unpredictable elements can be controlled statistically. We will use the ARIMA approach to analyze our data to control for the effects of variability. Additionally, we will also ensure that any variability that may occur will not be due to unreliability of the measurements (*i.e.*, outcomes will be measured objectively and assessed blindly). Lastly, the ITS methodology largely limits the generalizability of its findings [44]. However, the ITS design is a useful and pragmatic tool, particularly for pilot studies where initial evaluations of interventions and their refinement need to be done before the testing of the tool on a wider scale is justified. Furthermore, results from ITS studies can serve to inform the investigation of mediating factors (for example, if the intervention is found to be more effective in one site but not in another) as well as more extensive tests of their replicability in a randomized controlled trial.

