#### Outcomes

Primary outcomes will be the initiation of appropriate osteoporosis investigations (*i.e.*, BMD testing) and treatment (*e.g.*, bisphosphonates, nutritional supplements such as calcium and vitamin D) during a patient visit. "Appropriate" osteoporosis management is defined as the recommendations outlined in current clinical practice guidelines from Osteoporosis Canada [12] and is represented by a disease-management algorithm programmed into the osteoporosis tool. Secondary outcomes will include fractures, the reason for the visit, number of patients who successfully complete the RAQ (defined as an electronic log generated by the tablet PC from patient-initiated RAQs), the mean time for patients to complete the RAQ, and the mapping of an osteoporosis care model for patients who will complete the RAQ (*i.e.*, documentation of what physicians do during the visit and subsequent visits with patients). Chart review will also consist of extraction of site-specific data, including the number of age-eligible patients/practice who had at least one visit during the intervention period, the number of patients who are at risk for osteoporosis, and the mean number of patients who were seen by their family physician within a two-week segment.

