#### Unit of analysis and data collection

Our unit of analysis will be based on the multiple baseline assessment of individual family practice sites rather than a single group of participants being tested repeatedly before and after the introduction of the intervention. The data set at each time point will consist of patient charts, which will represent the "episode of care" used to extract outcome data for the study. To ensure the completeness and validity of the data set at each time point, we will apply the quality-control criteria of ITS designs by Ramsay *et al.*, which recommend that 80%-100% of the total number of episodes of care (*i.e.*, patient charts) be used in the data collection [27].

Once the intervention is implemented, data will be collected on all outcomes from electronic patient records (*i.e.*, PracticeSolutions^®^) and the touch-screen tablet PCs. The purpose of the pre-intervention chart review will be to establish a stable baseline of standard practice for each site. Visit-specific data (*e.g.*, initiation of osteoporosis disease management, reason for visit) will be collected bimonthly at each site by two researchers (MK and CM). To minimize the introduction of contamination that could bias results during this phase, all data collection techniques, procedures, and data collection forms will be standardized. For calibration of reliability, these two researchers will extract data from 10 randomly selected patient charts in duplicate until their agreement reaches ≥80%, at which point they will abstract data independently. The two researchers will collect data from the touch-screen tablet PCs, which will automatically generate two electronic logs each time a patient completes the RAQ. The first log will outline dated/timed RAQ responses, and the other will summarize the content of the BestPROMPT sheet. These electronic logs will be matched against patient-visit chart data to verify the use of the tool during the visit and to map any actions taken by the physician in response to the use of the RAQ.

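### Outcomes are said to be assessed blindly, but as described the two abstractors know the study period and are not shielded from the tool logs

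*Protocol article*

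**What the plan says.** Under Instability, the protocol article supports its claim that variability will not come from unreliable measurement by stating that "outcomes will be measured objectively and assessed blindly".

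Under Unit of analysis and data collection it describes how the data are gathered:

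- Visit-specific data, including initiation of osteoporosis management, "will be collected bimonthly at each site by two researchers".
- Those same researchers also handle the tablets: "The two researchers will collect data from the touch-screen tablet PCs, which will automatically generate two electronic logs each time a patient completes the RAQ".
- One log holds the patient's answers with date and time; its companion shows what the physician was recommended to do.
- On how the logs are then used, the article says: "These electronic logs will be matched against patient-visit chart data to verify the use of the tool during the visit". A second stated purpose of the matching is to map what the physician did in response to the questionnaire.
- For calibration, the two researchers will "extract data from 10 randomly selected patient charts in duplicate until their agreement reaches ≥80" per cent. After that, each works alone without further duplicate extraction being mentioned.

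Under Outcomes: "Primary outcomes will be the initiation of appropriate osteoporosis investigations" and treatment. What counts as appropriate is set by national guidelines, as represented in the tool's own algorithm.

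Two further safeguards are stated. Collection procedures and forms are standardised. Under Potential limitations, the plan undertakes to keep observers, databases and instruments consistent and to watch for changes.

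**The concern.** A claim of blinded assessment tells the reader that whoever recorded the outcome could not be influenced by knowing whether the tool was in use. Here the people who abstract the outcome also handle the material that reveals tool use, and the article describes nothing that keeps the two apart.

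This matters more in an interrupted time series than in many designs. The effect is read from a change between the pre- and postintervention segments. If charts are read more or less thoroughly, or appropriateness is judged with more information, once the tool is in place, that change in measurement starts at the same time as the intervention. The published report would meanwhile describe the outcomes as blinded and reliable.

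The calibration step is the one quantitative check on the abstractors, so it is natural to ask whether it would reveal disagreement about the primary outcome.

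**Working it through.** **1. Is the assessment blind?** No arithmetic applies; the stated property is set against the described procedure.

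| Blind to | What the article describes | Result |
|---|---|---|
| Study period | Each visit belongs to a dated two-week segment; the researchers collect the data at the sites | Not blind |
| Tool use at the visit | The same two researchers collect the logs, which are dated, show the recommendation content and exist only after introduction | Not protected |
| Separate assessor, masking or order of work | None described | Nothing restores blinding |

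**2. What would unequal ascertainment do?** Suppose abstraction finds a fraction Se_pre of true initiations before the interruption and Se_post after it, with no false positives. Then

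measured post/pre ratio = true ratio × Se_post / Se_pre.

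If the two fractions are equal, the ratio is unaffected. If not, a step appears at the interruption. As an assumed illustration only, 0.85 before and 0.95 after gives 0.95/0.85 = 1.12; the reverse gives 0.85/0.95 = 0.89. The article supplies neither figure, so direction and size are unknown. The planned ARIMA and regression models address trend, seasonality and random error. A step in measurement at the interruption is none of these and would be counted in the level change.

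**3. What does the calibration rule say about initiations?** The 80% threshold is a chosen value with no derivation, so there is nothing to reproduce. Inputs:

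- n = 10 charts and a threshold of 8/10, from the data collection section.
- Agreement scored as simple percent agreement per chart on one item: an assumption, because the article does not define it.
- Initiation rate p per visit: not given, so taken from 5% to 30%.

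With X ~ Binomial(10, p):

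- P(sample holds no initiation) = (1 − p)^10
- P(an abstractor who never records an initiation passes one round against a perfect one) = P(X ≤ 2)

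| p | No initiation in 10 charts | Never-recorder passes one round |
|---|---|---|
| 5% | 0.95^10 = 60% | 98.8% |
| 10% | 0.90^10 = 35% | 93.0% |
| 20% | 0.80^10 = 11% | 67.8% |
| 30% | 0.70^10 = 3% | 38.3% |

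The never-recorder is a deliberate extreme that marks the limit of what the rule can let through. A milder case: each abstractor flags one chart, and the two charts differ. Agreement is 8/10 = 80%, a pass with no shared event. Expected agreement is 0.1 × 0.1 + 0.9 × 0.9 = 0.82, so kappa = (0.80 − 0.82)/(1 − 0.82) = −0.11.

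A result of exactly 8/10 has an exact 95% confidence interval for true agreement of 44% to 97%.

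**The case against.** The strongest reply is that the article is a condensed account. Masking mechanics and order of work usually sit in an abstraction manual, and abstraction before matching is compatible with the text. A reader might infer that the abstractors match the logs themselves and have them open while recording the primary outcomes. The article does not say so: it puts the matching in the passive voice, with no actor or timing, and one stated purpose, mapping physician actions, serves a secondary outcome. That part of the reply stands. It does not rescue the blinding claim, because the article does say that the same two people collect the logs, and period is visible whatever the order of work.

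Outcomes also come from a single electronic record system shared by all sites, are described as objective, and are judged against a programmed algorithm. Forms are standardised, and instrumentation is named as a threat to be monitored. So the 10-chart exercise is not the only safeguard, and room for abstractor judgement is limited. This reduces the likely harm but does not make the assessment blind. The outcome also includes nutritional supplements and a judgement of appropriateness, either of which may need interpretation of the chart.

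On calibration, a reader might infer that initiations are rare and the rule is therefore empty. The article gives no rate, and with supplements counted as treatment a rate above 10% cannot be excluded. At 30% only 3% of samples would hold no event. If a kappa of at least 0.80 was meant, this part falls. Using kappa for the qualitative coding in phase 3 does not oblige the plan to use it here.

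**Conclusion.** The blinding claim does not match the described procedure. Assessment cannot be blind to period and, as written, is not protected from knowledge of tool use. This rests on the text alone and needs no assumed figures.

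Any resulting ascertainment difference would coincide with the interruption and could not be separated from a true effect by the planned analysis. It is tempting to add that the bias favours the tool, or to attach a size to it. The article supports neither: any pair of before-and-after sensitivities would be the reader's own.

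The calibration point is secondary and conditional. It needs simple percent agreement and a low event rate. It is material at 5% to 10% (60% to 35% of samples without an initiation), weaker at 20% (11%) and slight at 30% (3%).

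The whole point should be dealt with before data collection. It is not a reason to reject the design.

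**What to change.** 1. In each collection round, abstract and lock the primary outcomes before the tablet logs are opened or matched. Use structured fields of the electronic record where they exist, in the same way before and after the interruption.
2. Under Instability, replace the blinding statement with *abstracted blind to the tool logs, not to period*.
3. State that the agreement threshold is percent agreement, if that is meant. Include charts with initiations in the calibration set, and report agreement on positive charts, for example 2a/(2a + b + c), where a is the number of charts that both abstractors flag and b and c are the numbers flagged by only one. In the example with one different chart each, this is 0/(0 + 1 + 1) = 0, although overall agreement is 80%.

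The cost is a fixed order of work, a few lines in the abstraction manual and a few more duplicate charts by the same two abstractors. No new data source, staff or larger sample is needed.
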